## Abstract

**Background::**

Breast cancer (BC) poses a tremendous threat to the health of women worldwide, especially triple-negative breast cancers (TNBCs). Currently, the curative effect of traditional Chinese medicine (TCM) has been recognized in more and more people worldwide; however, the specific effect has not been systematically evaluated. The purpose of this cohort study is to evaluate the clinical effects of TCM syndrome differentiation on recurrence and metastasis rate, survival rate, and the quality of life in patients with TNBC.

**Methods::**

This study is a multicenter observational cohort trial taking 2 years. A total of 620 patients will be allocated at a ratio of 1:1 to receive TCM or not. The primary outcomes are progression-free survival (PFS) and overall survival (OS), which are calculated at the end of the trial. Secondary outcomes include TCM symptoms, Karnofsky Performance Status (KPS), ECOG score, European Organization for Research and Treatment of Cancer (EORTC) Breast-Cancer-Specific Quality of Life Questionnaire (EORTC QLQ-BR23), as well as clinical indicators including tumor markers, immune function evaluation, chest computed tomography/magnetic resonance imaging, and abdominal B-ultrasound. Assessments will be performed at baseline and 3, 6, 9, 12, 16, and 20 weeks after observation.

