### Sample size

2.2

Considering the results of the study at MD Anderson Cancer Center in foreign countries^[15]^ showed that the 3-year survival rate of TNBC patients was significantly shorter than that of non-TNBC patients (74% vs 89%, *P* < .01), as well as the lost rate of 20%, the sample size (N) is calculated by the following formula: 
[figure not shown]

*P*_0_ means the recurrence and metastasis rate of the nonexposed group; *P*_1_ represents the recurrence and metastasis rate of the TCM exposure group, *P*_1_ = RR × *P*_0_, where RR is the relative risk caused by exposure factors.

This study assumes that α = 0.05 and β = 0.10. According to the related study, the rate of recurrence and metastasis was 12% in the TCM group and 33.33% in the western medicine treatment group, respectively. The relative risk (RR) of TCM intervention was that RR = 12%/33.33% = 0.36. Domestic and foreign data showed that the 2-year recurrence and metastasis rate of TNBC patients was 17%, so *P*_0_ = .17, *P*_1_ = RR × *P*_0_ = 0.06.

Substituting the formula, the calculated amount of each group is as follows: 

Considering the 20% of drop rate, the confinement factor in different hospitals increased by 10% of the sample size, that is, at least 249 (N ≥ 249) cases should be observed in each group. Then, combined with the study period and the target population distribution of the study unit, 310 cases should be included in the Chinese medicine and Western medicine groups, respectively, in this study.

Before the research, investigators are responsible for the introduction the clinical research related matters and the records of the baseline data, then all participants sign the informed consent form. Patients in the TCM exposure group take Chinese medicine (San Yin Decoction) as well as original Western medicine, while patients in the nonexposed group only receive Western medicine treatment. The study will be performed during 2 years, and all results are recorded according to the Case Report Form (CRF).

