#### Primary outcomes

2.3.1

Primary outcomes include progression-free survival (PFS): the time from treatment to disease recurrence or death due to disease progression; and OS: the time from the beginning of treatment to death due to any cause. These 2 indicators are calculated at the end of the trial.

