### Statistical analysis

2.6

SPSS 18.0 (SPSS, lnc., Chicago, IL), Stata10.0 (StataCorp, College Station, Texas), and other statistical software are used for data analysis with a 2-sided significance level of 0.05, the point estimate, and 95% confidence interval. If the data obey the normal distribution and the variance is homogeneous, data are expressed as the number of cases (n) and the mean ± standard deviation (SD). Before and after treatment at multiple time points, measurement data using repeated measurement of variance analysis and multiple variance analysis are expressed as median (M), minimum (min), and maximum (max). The Kruskal–Wallis H test is used to compare the data between the 2 groups. The numerical variables are measured at multiple time points before and after treatment, and the generalized estimating equations or mixed effect models are used for the classification and sorting variables. If the analysis index is disordered using χ^2^ test, the analysis index is ordered with rank sum test, the 2-way ordered attribute of different data using linear χ^2^ test, and rank sum test. The survival rate is calculated by Kaplan–Meier method (K-M method), and the survival curve is drawn. Multivariate data are analyzed using multiple linear regression analysis, COX regression analysis, trend testing, and so on.

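### PFS and OS are both primary under one undivided two-sided 0.05 with no success rule, and the 90% power calculation covers recurrence only, so OS power is not established and is probably low

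*Protocol article*

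**What the plan says.** The Abstract (Methods) names two primary outcomes: "The primary outcomes are progression-free survival (PFS) and overall survival (OS), which are calculated at the end of the trial". Section 2.3.1 repeats the pair and adds: "These 2 indicators are calculated at the end of the trial". Neither place ranks them or says what counts as a positive study.

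Section 2.6 sets one general level for all analyses; SPSS, Stata and other packages "are used for data analysis with a 2-sided significance level of 0.05". It gives no split and no testing order.

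Section 2.2 sets the design error rates: "This study assumes that α = 0.05 and β = 0.10". The quantity being powered is a proportion. P0 "means the recurrence and metastasis rate of the nonexposed group", and P1 is the same rate under TCM. The inputs are a 2-year control rate ("Domestic and foreign data showed that the 2-year recurrence and metastasis rate of TNBC patients was 17" per cent) and an effect ("The relative risk (RR) of TCM intervention was that RR = 12%/33.33% = 0.36"). The result is at least 249 per group, raised on practical grounds to 310. The section also cites a 3-year survival of 74% in TNBC against 89% in non-TNBC, but neither figure enters the formula.

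**The concern.** With two primary endpoints, one undivided level and no success rule, a reader of the results cannot tell whether one significant endpoint out of two would be reported as a benefit. If it would, the study's error rate is not the stated 5%.

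The second problem is one of power. OS has primary status, but the document gives no assumed OS effect, number of deaths or power. Patients enter after surgery and free of recurrence (section 2.5), and the whole study lasts 2 years, so deaths may be few. A non-significant OS result could then be read as a failed primary outcome although the study was not sized for it. The Background says the study is meant to give strong evidence on both disease-free and overall survival, so the status of OS matters for the conclusions.

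**Working it through.** **1. Reproducing the plan's 249 (section 2.2).** Inputs: P0 = 0.17; P1 = 0.36 × 0.17 = 0.0612; two-sided alpha 0.05; power 0.90; 20% loss; 10% centre allowance. The printed formula is not legible in the text at hand, so two standard forms were tried.

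- Pooled variance under the null: n = [1.960·√(2p̄(1−p̄)) + 1.282·√(P0(1−P0)+P1(1−P1))]² / (P0−P1)², with p̄ = 0.1156. This gives n = 179.4, so 180, and 180/0.80 × 1.10 = 247.5.
- Pooled variance in both terms: n = 181.5, and 181.5/0.80 × 1.10 = 249.6.

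Both agree with 249. The whole two-sided 0.05 was therefore spent on the recurrence proportion, and nothing was reserved for OS.

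**2. Type I error.** Take two two-sided tests at 0.05, with bivariate normal statistics of correlation ρ and no effect on either endpoint. The chance of at least one significant result is 1 − P(|Z1| < 1.96 and |Z2| < 1.96).

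| ρ | Either endpoint suffices |
|---|---|
| 0 | 9.75% |
| 0.5 | 9.1% |
| 0.7 | 8.3% |
| 0.8 | 7.8% |
| 0.9 | 7.0% |

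If both must be significant, the error is at most 5%. The value of ρ is an assumption. PFS as defined in 2.3.1 counts deaths from disease progression, which are also OS events, so ρ = 0 is not realistic.

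**3. Control mortality over 2 years.** The document does not give it. Two routes from its own figures:

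- From 74% survival at 3 years with a constant hazard: 1 − 0.74^(2/3) = 18.2%. This exceeds the 17% two-year recurrence in section 2.2, although patients enter recurrence-free.
- From 17% recurrence at 2 years, followed by the average survival of about 2 years in late-stage disease (Background). Assumptions: constant hazards, recurrence treated as late stage, no other deaths. λ1 = −ln(0.83)/2 = 0.0932; λ2 = 1/2. Mortality = 0.17 − [λ1/(λ2−λ1)]·(0.83 − e^(−1)) = 0.17 − 0.229 × 0.462 = 6.4%. If the 2 years is read as a median (λ2 = ln 2/2), it is 4.9%.

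A range of 5 to 10% is therefore used as the assumption.

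**4. OS power.** Expected deaths d = n·[m + 1 − (1−m)^HR]; power = Φ(½·√d·|ln HR| − 1.96). Evaluable n = 310 × 0.80 = 248 per group, all followed for 2 years. The hazard ratios are assumptions; 0.36 carries the recurrence relative risk over to OS unchanged.

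| HR | m = 5%: deaths, power | m = 10%: deaths, power |
|---|---|---|
| 0.36 | 16.9, 56% | 34.0, 85% |
| 0.5 | 18.7, 32% | 37.5, 56% |
| 0.7 | 21.1, 13% | 42.4, 21% |

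For comparison, 90% power needs about 41 deaths at HR 0.36, 88 at HR 0.5 and 331 at HR 0.7.

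**5. Cost of splitting alpha.** At two-sided 0.025 the first formula in step 1 gives n = 212.1 per group, and 212.1/0.80 × 1.10 = 291.7, so about 292, below 310. With 248 evaluable, recurrence power is 96.8% at 0.05 and 94.2% at 0.025.

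**The case against.** The strongest reply is that section 2.6 states a general level and does not assign 0.05 to each endpoint. An analysis plan that is not shown could set a testing order, a split or a both-must-succeed rule, and an article may leave that to it. This stands in part: the missing rule alone would be a thin point, and no inflation can be asserted as fact. But choosing the primary endpoints and sizing the study for them is protocol content, and sections 2.2 and 2.3.1 have made those choices. A later testing rule would not make the calculation in 2.2 cover OS.

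A reader might infer that the false-positive rate approaches 10%. The documents do not support that. It is the ceiling for independent tests under an either-endpoint rule that is nowhere stated, and these endpoints share patients and deaths.

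A reader might also infer that OS lacks the power the plan claims for it. No OS power is claimed, since beta = 0.10 is tied to recurrence. Low OS power also depends on assumptions. With 18.2% mortality, HR 0.36 and full follow-up, 248 to 310 per group would give 98 to 99.5%. At HR 0.5 that mortality gives 82 to 90%. However, it means more deaths than the plan's own expected recurrences, so it sits badly with section 2.2. At 10% mortality, 90% is passed only with HR 0.36 and all 310 per group evaluable (42.5 deaths, about 91%).

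Finally, the 74% against 89% comparison is background and not a misused OS effect, because it does not enter the formula.

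**Conclusion.** The point holds in this form. Two primary endpoints share one undivided two-sided 0.05 with no success rule, and the full alpha and the 90% power belong to the 2-year recurrence and metastasis proportion alone.

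The error rate depends on the unstated rule: about 7 to 9% if either endpoint suffices and the test statistics correlate at 0.5 to 0.9, and no more than 5% if both are required. OS power is not established and is probably low under the plan's own recurrence inputs. Even if the large recurrence effect carried over in full, it would be about 56 to 85% at 5 to 10% control mortality. Follow-up per patient is not stated; if recruitment takes up part of the 2 years, there would be fewer deaths and lower power.

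This should be corrected. The design does not have to be enlarged to do so.

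**What to change.** - **Section 2.3.1:** name the recurrence-based endpoint as the single primary outcome, under one definition. The Background speaks of DFS, 2.3.1 of PFS, and 2.2 powers a proportion. Make OS the key secondary outcome.
- **Section 2.6:** state that the primary is tested at two-sided 0.05 and that OS is tested at 0.05 only if the primary is significant. This fixed sequence holds the overall error at 5%.
- **Section 2.2:** state that beta = 0.10 applies to recurrence only.

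The cost is about one sentence in each section and no extra patients. The downside is that no formal OS claim is possible if the recurrence endpoint fails.

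If the sponsor prefers to keep both primary, a 0.025/0.025 split also holds the error at 5% or below. It needs about 292 per group for recurrence after the plan's own inflation, within the planned 310. The price is slightly lower recurrence power (94.2% instead of 96.8% with 248 evaluable) and a stricter level for OS. It would not repair OS power, so an event-based OS power statement with its assumed mortality and hazard ratio should then be added.

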**Discussion::**

This will be the first clinical trial to evaluate the PFS and OS in TNBC patients receiving TCM, which may be used to assess the feasibility of a larger-scale clinical trial in the future, and formulate a standardized TCM treatment plan.

**Study registration::**

ClinicalTrials.gov (NCT03332368).

## Background

1

Breast cancer (BC) is one of the most serious threats to women's health in China, and is the most common causes of cancer death of women in the world.^[1]^ The negative immunohistochemical detection results of estrogen receptor (ER), progesterone receptor (PR), human epidermal growth factor receptor-2 (Her-2) are defined as triple-negative breast cancer (TNBC).^[2]^ Compared with other types of BC, TNBC has a high risk of invasion, local recurrence, and metastasis. Moreover, endocrine therapy and Her-2 target therapy are not suitable for patients with TNBC.^[3,4]^ Meanwhile, due to high cost of biological agents, chemotherapy is still a widespread treatment for most of patients without medical insurance in China. The incidence of TNBC is getting younger and younger.^[5]^ Once the disease progress to the late stage, it is more difficult to control, and the average survival time is only about 2 years.^[6]^

Fortunately, due to the impact of traditional Chinese medicine (TCM) treatment in China, the majority of postoperative TNBC patients have received varying degrees of TCM treatment.^[7,8]^ On the basis of previous multicenter, randomized, double-blind, and controlled research, TCM can improve the quality of life of TNBC patients, as well as regulate immune function,^[9]^ inhibit tumor growth,^[10]^ reduce recurrence and metastasis,^[11]^ and extend the survival time compared to chemotherapy drugs and molecular targeted drugs. In addition, compared with the biological agents, TCM prices are relatively low.^[12]^

TCM treatment has a long history and has been proved to have obvious therapeutic effects. Clinical study has found that the 5-year recurrence and metastasis rate is significantly lower in the TCM treatment group than that in the simple Western control group.^[13]^ In addition, a high dose of TCM Decoction has a similar killing effect on MDA-MB-435 compared with cyclophosphamide; meanwhile, TCM Decoction can reduce the expression of vascular endothelial growth factor (VEGF) and its receptors FlK-1 in BC tumor tissue, indicating that TCM has an important role in anti-tumor and anti-metastasis effects.^[14]^

The purpose of this study is to evaluate whether the intervention of TCM can improve the postoperative TNBC patients with disease-free survival (DFS) and overall survival (OS), and then provide strong evidence that TCM treatment has exact effects and obvious advantages. Meanwhile, this study can establish TNBC patient information database, which may contribute to the correct guideline for TNBC patients with TCM treatment, build harmonious relationship between doctors and patients, increase TNBC patients’ compliance, and enhance the confidence to overcome the disease.

## Methods

2

### Design

2.1

The study is a multicenter observational cohort trial lasting 2 years in 5 locations, including Longhua Hospital affiliated to Shanghai University of TCM, Shuguang Hospital affiliated to Shanghai University of TCM, Yueyang Hospital of integrated Chinese and Western Medicine, Zhejiang Provincial Hospital of TCM, and Fudan University Shanghai Cancer Center. All the eligible TNBC patients are divided into 2 cohorts: TCM exposure group and nonexposed group, according to whether taking TCM treatment (Fig. 1). Participants in the nonexposed group receive preoperative chemotherapy and/or radiotherapy, as well as postoperative biological agents after surgery, according to the National Comprehensive Cancer Network (NCCN) Breast Cancer Treatment Guidelines. Participants in the TCM exposure group receive TCM combined with Western medicine treatment. TCM treatment is based on syndrome differentiation by inspection, listening and smelling, interrogation, pulse-taking, and palpation, and then provide the most appropriate decoction.

**Figure 1 F1:**
[figure not shown]
Flow chart of the study.

### Sample size

2.2

Considering the results of the study at MD Anderson Cancer Center in foreign countries^[15]^ showed that the 3-year survival rate of TNBC patients was significantly shorter than that of non-TNBC patients (74% vs 89%, *P* < .01), as well as the lost rate of 20%, the sample size (N) is calculated by the following formula: 
[figure not shown]

*P*_0_ means the recurrence and metastasis rate of the nonexposed group; *P*_1_ represents the recurrence and metastasis rate of the TCM exposure group, *P*_1_ = RR × *P*_0_, where RR is the relative risk caused by exposure factors.

This study assumes that α = 0.05 and β = 0.10. According to the related study, the rate of recurrence and metastasis was 12% in the TCM group and 33.33% in the western medicine treatment group, respectively. The relative risk (RR) of TCM intervention was that RR = 12%/33.33% = 0.36. Domestic and foreign data showed that the 2-year recurrence and metastasis rate of TNBC patients was 17%, so *P*_0_ = .17, *P*_1_ = RR × *P*_0_ = 0.06.

Substituting the formula, the calculated amount of each group is as follows: 

Considering the 20% of drop rate, the confinement factor in different hospitals increased by 10% of the sample size, that is, at least 249 (N ≥ 249) cases should be observed in each group. Then, combined with the study period and the target population distribution of the study unit, 310 cases should be included in the Chinese medicine and Western medicine groups, respectively, in this study.

Before the research, investigators are responsible for the introduction the clinical research related matters and the records of the baseline data, then all participants sign the informed consent form. Patients in the TCM exposure group take Chinese medicine (San Yin Decoction) as well as original Western medicine, while patients in the nonexposed group only receive Western medicine treatment. The study will be performed during 2 years, and all results are recorded according to the Case Report Form (CRF).

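### PFS and OS are timed from an unidentified treatment start that, read literally, can precede enrolment, so recurrence-free time guaranteed by the entry criteria may count as follow-up, unequally in two non-randomised cohorts

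*Protocol article*

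**What the plan says.** **Time origin.** Section 2.3.1 (Primary outcomes) defines PFS as "the time from treatment to disease recurrence or death due to disease progression" and OS as "the time from the beginning of treatment to death due to any cause". Neither definition says which treatment is meant.

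**What treatment covers.** Section 2.1 (Design) says of the comparison cohort: "Participants in the nonexposed group receive preoperative chemotherapy and/or radiotherapy, as well as postoperative biological agents after surgery". Of the other cohort it says: "Participants in the TCM exposure group receive TCM combined with Western medicine treatment". Section 2.2 (Sample size) adds: "Patients in the TCM exposure group take Chinese medicine (San Yin Decoction) as well as original Western medicine".

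**Who is enrolled and when.** Section 2.5 (Inclusion and exclusion criteria) admits patients who have had surgery for primary breast cancer and have no recurrence or metastasis. Cohorts are formed by whether the patient takes TCM (section 2.1), not by randomisation. Section 2.2 gives an order of events, starting with introduction of the study and "records of the baseline data, then all participants sign the informed consent form"; it then describes what each group takes.

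**Analysis.** Section 2.6 (Statistical analysis) lists Kaplan–Meier estimation and Cox regression.

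**The exposure itself.** The abstract's stated purpose is to "evaluate the clinical effects of TCM syndrome differentiation on recurrence and metastasis rate", and section 2.1 says: "TCM treatment is based on syndrome differentiation by inspection, listening and smelling, interrogation, pulse-taking, and palpation, and then provide the most appropriate decoction". Section 2.2 names a single formula, San Yin Decoction.

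**The concern.** The stated origin allows at least three readings:

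- **First Western treatment or surgery.** Both lie before enrolment for everyone, since entry is postoperative.
- **Start of TCM.** Nonexposed patients have no such date, so the cohorts would need different origins. The Background section says that most postoperative TNBC patients have already received some TCM, so this date too may precede enrolment.
- **Start of the study period**, at or just after enrolment.

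Under the first two readings, a patient who recurred between the origin and enrolment could not have entered the study. That interval is event-free because of the selection rule, yet a Kaplan–Meier or Cox analysis on this clock, without delayed entry, would count it as time at risk. In a randomised trial the interval would balance on average. Here nothing in the design makes it equal. The cohort with the longer interval looks better than it is, and a larger sample does not remove the error. Both primary outcomes use this origin.

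**Working it through.** **1. The plan's own figure.** This point does not dispute the sample size; it supplies the inputs. From section 2.2: P0 = 0.17, RR = 0.36, so P1 = 0.36 × 0.17 = 0.0612; α = 0.05 (two-sided by section 2.6) and β = 0.10. The printed formula is not visible. With the simple pooled form, mean p = (0.17 + 0.0612)/2 = 0.1156, and n = 2 × 0.1156 × 0.8844 × (1.960 + 1.282)² / 0.1088² = 181.5. Then 181.5 × 1.1 / 0.8 = 249.6, against the stated 249. The figure reproduces.

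**2. Inputs for the illustration.**
- From the plan: 17% two-year risk; 310 per group; 20% loss, so 310 × 0.8 = 248 evaluable per group.
- Assumed: no true TCM effect, constant hazard, and the gap m (months from clock start to enrolment). The article gives no gap for either cohort.

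**3. Formula.** Hazard λ = −ln(1 − 0.17)/24 = 0.00776 per month. If the first m months on the clock are event-free by selection, the apparent 24-month risk is 1 − exp(−λ(24 − m)):
- m = 0: 0.1700
- m = 3: 0.1504
- m = 6: 0.1304

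**4. Worked case, 6 months (exposed) and 3 months (nonexposed).** RR = 0.1304/0.1504 = 0.87. Difference = 0.0200, mean p = 0.1404, SE = √(2 × 0.1404 × 0.8596/248) = 0.0312, and difference/SE = 0.64. The two-sided 5% test then rejects with probability Φ(0.64 − 1.96) + Φ(−0.64 − 1.96) ≈ 0.098.

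**5. Other gaps, same method.**

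| Gap exposed / nonexposed (months) | Null RR | False-positive chance |
|---|---|---|
| 3 / 3 or 6 / 6 | 1.00 | 5.0% |
| 6 / 3 | 0.87 | 9.8% |
| 3 / 6 | 1.15 | 9.8% |
| 1 / 0 | 0.96 | 5.4% |
| 3 / 0 | 0.88 | 9.1% |
| 6 / 0 | 0.77 | 23.4% |

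**6. Checks under other models.**
- Person-time, with two years' observation from enrolment: expected time at risk after enrolment is 0.17/0.0932 = 1.825 years. Adding the gaps gives a rate ratio for 6 / 3 of (1.825 + 0.25)/(1.825 + 0.50) = 0.89.
- Cox simulation, 248 per group, 3,000 runs, clock at treatment: 6 / 3 gives HR 0.85 with about 10% rejections, and 6 / 6 gives HR 1.00 with about 5%.
- With the clock moved to enrolment, even the 6 / 0 case returns to HR 0.99 with 4.9% rejections.

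The calculations use the recurrence risk, so they describe PFS. The mechanism is the same for OS, because patients must be alive to enrol, but the article gives no two-year death rate from which to size it.

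**The case against.** The best defence is that treatment means the study treatment period. Section 2.3.2 compares symptom scores before and after treatment, which presupposes a study baseline measurement before treatment begins. Section 2.6 uses the same phrasing for repeated measurements, the abstract schedules assessments from baseline, and section 2.2 describes baseline recording and consent before saying what each group takes. On that reading there is no pre-enrolment gap. The preoperative therapy in section 2.1 could be background care, not a clock start. This is a fair reading and may be the intended one, but section 2.3.1 does not adopt it, and the text does not exclude the others.

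It is also right that every gap length above is assumed, and that a limit on time since surgery could sit in the full protocol. The absence of such a limit is therefore not part of this point.

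Two stronger inferences should be resisted:

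- **That the plan contains a bias in favour of TCM of the order of RR 0.77 with 23% false positives.** That needs a gap in the exposed cohort only. Both cohorts enrol after surgery, so a common anchor at surgery or first Western treatment gives both a gap. A one-sided gap needs different anchors, and no section states that. Nothing in the text shows that the gaps differ, or in which direction.
- **That the article contradicts itself on the exposure.** A named base formula modified by syndrome fits both section 2.1 and section 2.2. The article does not say so, which makes this a request for one clarifying sentence.

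**Conclusion.** The point stands as a badly fixed definition, not as a demonstrated bias. Both primary outcomes start at a treatment that the article does not identify; read literally, it can precede an enrolment that requires freedom from recurrence, in cohorts that are not randomised. If the gaps are unequal, the contrast is biased in a direction that the text does not reveal. A three-month difference (6 against 3 months) moves the null risk ratio to about 0.87 or 1.15 and roughly doubles the 5% error rate. Equal gaps or an enrolment clock leave it at 1.00, and a one-month difference is negligible. These sizes rest on assumed gaps, a constant hazard, the plan's 17% risk and 248 evaluable per group. It should be corrected because the remedy is cheap. Confidence is medium, since enrolment may already be the intended origin.

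**What to change.** - In section 2.3.1, define PFS and OS as running from the date of the enrolment visit in both cohorts.
- In section 2.1, set cohort membership by the patient's TCM status at that visit.
- Record time since surgery at baseline and include it as a covariate in the Cox regression that section 2.6 already lists, because recurrence risk may change with time since surgery.
- As a minor wording point, state in section 2.2 whether San Yin Decoction is the base formula of the syndrome-differentiated treatment. The clinical content is for the investigators to decide.

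**Cost.** Protocol wording and one or two baseline CRF items, with no extra patients or visits. Recruitment has begun, so surgery dates may have to be added for patients already enrolled. Survival times counted from enrolment will be slightly shorter than those counted from first treatment. If enrolment was always the intended origin, one sentence settles the clock. The change does not deal with confounding between users and non-users of TCM, or with differences in how long patients had used TCM before entry.

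### Power is based on 24-month recurrence risks, but a 2-year study that includes recruitment gives most patients less than 24 months of follow-up

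*Protocol article*

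**What the plan says.** All references are to the protocol article.

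- **Sample size (2.2), error rates.** "This study assumes that α = 0.05 and β = 0.10". Statistical analysis (2.6) works "with a 2-sided significance level of 0.05".
- **Sample size (2.2), risks.** The unexposed risk P0 comes from a 24-month figure: "Domestic and foreign data showed that the 2-year recurrence and metastasis rate of TNBC patients was 17" per cent. The exposed risk is P0 times a relative risk: "The relative risk (RR) of TCM intervention was that RR = 12%/33.33% = 0.36". This gives P1 = 0.06.
- **Sample size (2.2), numbers.** After allowances of 20% for dropout and 10% for differences between hospitals, the minimum is 249 per group. The plan then goes to 310 per group, with reference to the study period and the distribution of patients.
- **Study length.** Design (2.1): "The study is a multicenter observational cohort trial lasting 2 years in 5 locations". Sample size (2.2): "The study will be performed during 2 years, and all results are recorded according to the Case Report Form (CRF"). The Abstract also gives 2 years.
- **Analysis time.** Primary outcomes (2.3.1), on PFS and OS: "These 2 indicators are calculated at the end of the trial".
- **Recruitment.** Trial status (4) says that recruitment began in January 2017. The article gives neither an end of recruitment nor a minimum follow-up per patient.

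**The concern.** P0 and P1 are the risks that a patient has accumulated after 24 months. Using them in the sample size means that every evaluable patient is observed for that long. The article gives 24 months as the length of the study, fixes the calculation of PFS at its end, and treats the start of recruitment as an event within the trial. On that reading only the first patients enrolled reach 24 months. With uniform entry the average potential follow-up is 18 months if accrual takes 12 months, and 12 months if it takes 24.

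Shorter follow-up means fewer recurrences. Kaplan-Meier and Cox analyses draw their precision from the number of events, so the power attached to the sample size would be too favourable by an amount that depends on accrual. The practical risk is a primary analysis with far fewer events than planned, in which an inconclusive result is read as coming from a study with 90% power.

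**Working it through.** **Inputs from the article:** two-sided alpha 0.05; beta 0.10; P0 = 0.17 at 24 months; RR = 0.36, so P1 = 0.36 × 0.17 = 0.0612 (printed as 0.06); 20% dropout; 10% hospital allowance; 249 and 310 per group; study length 24 months.

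**Assumptions, not in the article:** constant hazards; uniform accrual over A months; analysis at month 24; the 20% lost contribute nothing, as the plan's inflation treats them.

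**1. The plan's own figure.** The formula is an image that is not shown, so a standard form is used. The mean risk is (0.17 + 0.0612)/2 = 0.1156. Then n = 2 × 0.1156 × 0.8844 × (1.960 + 1.282)² / (0.1088)² = 181.5. Taking 181, 181/0.8 × 1.1 = 248.9, that is 249. The form with separate variances under the alternative gives 180, and 180/0.8 × 1.1 = 247.5. The stated 249 therefore reproduces.

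**2. Hazards.** The ratio is HR = ln(1 − 0.0612)/ln(1 − 0.17) = 0.06315/0.18633 = 0.339. Per month, λ0 = 0.18633/24 and λ1 = 0.06315/24.

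**3. Expected risk at month 24 with accrual over A months.** Averaging 1 − exp(−λu) over follow-up u from 24 − A to 24 gives 1 − [exp(−λ(24 − A)) − exp(−24λ)]/(λA). For P0 and A = 12: 1 − (0.9110 − 0.8300)/0.09317 = 0.130. For A = 24: 1 − (1 − 0.8300)/0.18633 = 0.088.

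**4. Events and power.** Evaluable patients per group are 0.8 × 310 = 248 and 0.8 × 249 = 199. Expected events are the evaluable number per group times the sum of the two risks. Power is from simulation of a two-sided log-rank test.

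| Accrual A (months) | Risks, unexposed / TCM | Events, 310 per group | Power, 310 | Events, 249 per group | Power, 249 |
|---|---|---|---|---|---|
| 0 | 17.0% / 6.1% | 57 | 0.97 | 46 | 0.94 |
| 6 | 15.0% / 5.4% | 51 | 0.96 | 41 | 0.91 |
| 12 | 13.0% / 4.6% | 44 | 0.92 | 35 | 0.85 |
| 18 | 10.9% / 3.9% | 37 | 0.88 | 29 | 0.79 |
| 24 | 8.8% / 3.1% | 29 | 0.79 | 24 | 0.70 |

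**5. Events needed for 90% power.** Schoenfeld: 4 × (1.960 + 1.282)² / (ln 0.339)² = about 36. Freedman: (1.960 + 1.282)² × (1.339/0.661)² = about 43 (44 with rounding up). At a hazard ratio this far from 1, Schoenfeld is optimistic: about 37 events gave a simulated power of 0.88.

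**6. Sensitivity.**
- *Dropout of 20% spread over time instead of lost outright:* 310 per group gives 0.99, 0.95, 0.92 and 0.84 for A = 0, 12, 18 and 24; 249 gives 0.96, 0.91, 0.85 and 0.76.
- *The 10% hospital allowance also treated as used up:* 310 × 0.8/1.1 = 225 per group gives 0.96, 0.89, 0.85 and 0.74 for the same A; 249 × 0.8/1.1 = 181 gives 0.91, 0.83, 0.75 and 0.66.

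**The case against.** **Recruitment may lie outside the 2 years.** A reader might take it as established that recruitment is included. It is not. Neither Design nor Sample size says so, and the 2 years could mean observation per patient. In that case the 24-month risks are appropriate. The calendar reading is still the more natural one, because it is the study that is said to last 2 years and the outcomes are tied to the end of the trial. If the other meaning was intended, the text needs to say it.

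**The study may well have its 90%.** A reader might conclude that the study is underpowered. The article does not support that. The 249 is a floor, and the planned number is 310. With 20% lost outright, 310 per group stays above 90% at 12 months of accrual and falls below it by 18. With gradual dropout it is still at 0.92 at 18 months. Section 2.2 also mentions the study period when it moves to 310, so follow-up may have been considered. No calculation is shown, however, and the risks in the formula remain 24-month risks.

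**The formula does no harm by itself.** It is tempting to say that a two-proportion formula for a time-to-event endpoint loses power. It does not: with full follow-up, 249 per group gives 0.94 by log-rank. The loss comes only from shortened follow-up.

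**An article may leave the accrual period to the full protocol.** That is fair, and its absence alone would not be a finding. What stands is that the inputs that are printed, a 24-month risk and a 2-year study analysed at its end, do not fit together unless accrual takes almost no time.

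**Conclusion.** The point holds conditionally. As section 2.2 is written, its power basis assumes 24 months of follow-up for everyone, while the stated study length and analysis time most naturally give most patients less. Expected events at 310 per group would fall from about 57 to about 44 with 12-month accrual and to about 29 with 24-month accrual, roughly half. Power would range from 0.97 down to 0.79, and at the stated minimum of 249 from 0.94 down to 0.70. The range exists because the accrual length is unknown. It also rests on constant hazards, uniform entry, the plan's own relative risk and 20% lost outright. The 249 is correctly computed from its inputs; the fault is in the time horizon of those inputs. The paragraph should be corrected, but this is no evidence that 620 patients are too few.

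**What to change.** Keep 620 patients and make one of two changes to section 2.2, with 2.3.1 brought into line:

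1. State that PFS is analysed when every patient has had the 24 months of follow-up that P0 assumes, and word the study length so that it covers recruitment plus that follow-up; or
2. Keep the present analysis date, state the accrual period and minimum follow-up, replace 17% and 6% by the risks expected under them, and give the expected number of events and the resulting power for 310 per group. For orientation, 90% power at the plan's own effect needs about 36 events by Schoenfeld and 43 to 44 by Freedman.

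The events figure should justify the power and should not become a stopping target. A fixed cut-off at 36 events would rest on the more optimistic formula. If it were triggered by whichever came first, events or follow-up, it could end the study early and shorten observation for OS, which is also primary.

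The cost is one rewritten paragraph and no extra patients. Under option 1 the analysis date may move later; under option 2 the stated power becomes less favourable if accrual is slow.
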